### **Withdrawal from Trial**

Following ACLR, each participant will have a scheduled follow-up visit at the HCTM Orthopaedic Outpatient Clinic. Every effort will be made to meet each participant's feasibility in attending the designated follow-up appointments (For example, flexible appointment times and dates). If they withdraw their consent, they will no longer be participants and will continue to receive the standard care rehabilitation and scheduled Orthopaedic Clinic follow-up. Information collected up to this point will be included.

### **Data Collection**

The study will collect demographic data, as well as pre-, intra-, and postoperative data (see Table 3). Data will be gathered from the participants and their medical records for all the data collection forms (see Appendix A, C, and D). Baseline evaluations will be conducted throughout the pre-operative period, within a range of 14 days, to reduce any bias when selecting participants. The subsequent assessment in the 4th week ( $\pm 14$  days), 8 weeks ( $\pm 14$  days), and three months ( $\pm 14$  days) are scheduled at the Orthopaedic Clinic (van Melick et al., 2021). The blinded assessors will give all tests and questionnaires in person, ensuring participant consistency. These assessments will take place at four weeks, eight weeks and three months after the surgery. Phone consultations will be used for post-hospital discharge follow-up. Participants who cannot be reached by phone for a continuous period of 14 days starting from the assessment due date will be classified as lost to follow-up for outcome measurement.

intra-reliability had a value of 0.9269 [95% C.I.: 0.8909–0.9533] (Grgic et al., 2020; Karagiannopoulos et al., 2022; Romero-Franco et al., 2019).

The participants are directed to generate deliberate isometric contractions of their quadriceps or hamstring muscles, by pushing against the resistance provided by the dynamometer's arm with a perceived maximal effort of 100% (Grgic et al., 2020). During the formal testing, the participants conducted three maximum voluntary isometric contractions (MVIC) of knee extension lasting five seconds each for the quadriceps (Padulo et al., 2020). Similarly, This is followed by knee flexion testing for the hamstrings. A minute rest time will be given between the quadriceps and hamstring testing (Mellemkjær et al., 2024).

The assessor will consistently give instruction and verbal encouragement (see Appendix I). The participants are instructed to exert maximum force by either pushing with their quadriceps or pulling with their hamstrings against the dynamometer. The average and best scores of the peak forces will be recorded (Grgic et al., 2020).

The average scores of quadriceps and hamstring muscular strength during rehabilitation are quantified using the Quadriceps Index (QI) and Hamstring Index (HI), which are calculated using the formula:  $(\text{MVIC peak force of the affected limb} / \text{MVIC peak force of the unaffected limb}) \times 100$  (van Melick et al., 2021).

### **Secondary/Explorative Outcomes:**

All trial participants will complete the International Knee Documentation Committee Subjective Knee Form (IKDC-SKF) questionnaire (Appendix B) to evaluate their perception of daily knee function and associated symptoms (Jeon et al., 2022; Roula et al., 2023). The IKDC, a free online patient-reported outcome questionnaire that does not require licensing for non-commercial research, evaluates three crucial aspects of the patient's condition: symptoms, athletic activity, and knee function. The questionnaire is self-explanatory, meaning that it is simple for patients to understand and complete on their own. It has been created and confirmed to be effective for the population undergoing ACL reconstruction and comprehensively covers The International Classification of Functioning, Disability and Health (ICF) domains (Zebis et al., 2019). The Intra-Class Correlation (ICC) of the IKDC showed acceptable validity and responsiveness. The subjective form achieved excellent scores for construct validity, with 84% confirmation of preset hypotheses, and responsiveness, with 86% confirmation, in its test-retest reliability assessment (Jeon et al., 2022; Richardson et al., 2023).

The Active Knee Extension Test (AKET) will use an inclinometer to assess participants' hamstring flexibility. It relies on measuring the knee extension angle (KEA). We determine the hamstring flexibility by recording the KEA value plus 90°. The participant lies supine, with their hip in a 90° flexion position and a flat position for the contralateral leg. They are asked to extend their knee until they feel maximum tightness in the posterior thigh without pain, maintaining a relaxed ankle position to reduce the impact of the gastrocnemius muscle. In the interim, the tester will ensure that the tested hip is in a 90° flexion position by reading the inclinometer on the thigh. One or more of the following three criteria can determine the endpoint for AKET: (a) the examiner's perception of firm resistance; (b) the visible onset of pelvic rotation; and (c) the participant experiencing a strong but tolerable stretch, slightly before the onset of pain. In a previous study (Niewiadomy et al., 2021), researchers proposed

a clinically significant improvement of 10.2°. The AKET has demonstrated high reliability in evaluating hamstring flexibility in healthy people, with intraclass correlation coefficients (ICC) of 0.87 for the dominant knee and 0.81 for the non-dominant knee, while the intra-rater (test-retest) reliability ICC scores varied between 0.75 and 0.97 (Olivencia et al., 2020).

### **Adherence monitoring**

A threshold for adherence is established for the experimental group, targeting participants to report a self-perceived rating of  $\geq 80\%$  (Cimino & Braun, 2023). Participants are advised to adhere to the instructions on home-based programs included in their respective flyers. The study used self-report scales and exercise diaries to measure adherence to the home exercise programme over 3 months. Participants are classified as adhered ( $\geq 3$  times per week) or non-adhered ( $\leq 2$  times per week) based on the average frequency of sessions performed weekly (Welling, 2024). Participants are instructed to complete the weekly exercise diary via online Google Form (see Appendix J). Physiotherapists will contact participants weekly via phone or WhatsApp to reinforce their exercise adherence. Self-report questionnaires and activity diaries have demonstrated efficacy, simplicity, and affordability as means of assessing exercise adherence in clinical and research contexts (Lahham et al., 2018; Nicolson et al., 2018).

The Sports Injury Rehabilitation Adherence Scale (SIRAS) is administered by a physician and physiotherapist to assess the level of adherence of all patients to the rehabilitation procedure in both study groups at the Orthopaedic Clinic and physiotherapy outpatient rehabilitation session (see Appendix E). The SIRAS is a reliable measure for evaluating clinic-based adherence in musculoskeletal rehabilitation with inter-rater and test-retest reliability coefficients ranging from 0.76 to 0.93 (Furlong & Hall, 2023).

ACL rehabilitation adherence and recovery can be significantly impacted by fear of movement, addressed by the Tampa Scale of Kinesophobia (TSK), a self-report checklist, utilising a 4-point likert scale (Ohji et al., 2022). By monitoring this fear, clinicians can improve compliance and modify rehabilitation programs (Kasmi et al., 2023). The TSK enables personalised treatment to overcome physical and psychological barriers. The TSK will be assessed preoperatively and at 3 months post-ACL reconstruction to monitor changes in fear of movement and reinjury (see Appendix F). The Tampa Scale of Kinesophobia (TSK) is available online for free use at <https://eprovide.mapi-trust.org/instruments/tampa-scale-for-kinesiophobia-11>, requiring only proper citation and acknowledgement in relevant publications or research (Woby et al., 2005).

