## **Specific Objectives**

1. To investigate the difference in hamstring strength between the ULIT and the standard care group compared to the standard care alone group at 4, 8, and 12 weeks post-ACLR.
2. To measure the changes in physical function based on the IKDC score in the ULIT group compared to the standard care group at preoperative and 12 weeks post-ACLR.
3. To evaluate the effect of ULIT on hamstring flexibility, measured by the active knee extension test (AKET) test, compared to standard care alone at preoperative and 12 weeks post-ACLR.
4. To analyse the relationship between patient adherence to ULIT and improvements in hamstring strength and physical function over the 12-week rehabilitation period.

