**Figure 9: Study Three (RCT) Flow Chart**

### Control group (Standard care)

Patients will be directed to follow the standard care ACLR rehabilitation protocol from preoperative until 12 weeks after the ACLR (see Figure 10). Both study groups will receive standard physiotherapy care from the Department of Medical Rehabilitation Services (HCTM). For standard care rehabilitation sessions, there are five physiotherapists in charge with more than five years of clinical expertise in musculoskeletal rehabilitation. Current rehabilitation strategies consist of knee mobilisation exercises, cryotherapy, and progressive resistance exercises, including eccentric strengthening exercises, proprioceptive training, and dynamic stabilisation drills. The standard outpatient physiotherapy program takes about one hour per session, with a recommendation of 1-2 sessions per week until three months post-operative.

All participants are encouraged to diligently follow the designated daily home exercise program. The standard care involves a personalised therapeutic exercise programme that is specifically designed to meet the needs of each client's goal and the timeline of ACLR recovery. This physiotherapy outpatient rehabilitation program lasts approximately one hour per session, with 1-2 attended sessions per week recommended until three months post-operative. Furthermore, all participants are instructed to diligently adhere to the prescribed daily home exercise programme (see Appendix H).

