### **Intervention Group (ULIT + Standard Care)**

A single physiotherapist will administer the ULIT. The treating physiotherapist will present the ULIT to patients in verbal, demonstration, and written formats. In the fourth week following ACLR surgery, the treating physiotherapist will conduct the ULIT as a single, personalised session. The treating physiotherapist will instruct patients to follow the ULIT from 4 to 12 weeks post-operatively together with the standard care ACLR rehabilitation protocol. The ULIT comprised three concise isometric exercises: 1) wall push-up, 2) shoulder extension, and 3) shoulder external rotation (see Appendix I). The intervention group will be instructed to continue the ULIT plus standard care rehabilitation daily as a warm-up and home exercise programme for eight weeks.

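### The adherence classes omit averages between 2 and 3 sessions a week, and the rule does not isolate the ULIT adherence that Specific Objective 4 is about

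*Protocol*

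**What the plan says.** Four parts of the protocol bear on this.

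- **Prescription.** Under Intervention Group, the physiotherapist will "instruct patients to follow the ULIT from 4 to 12 weeks post-operatively", and patients are told to "continue the ULIT plus standard care rehabilitation daily as a warm-up and home exercise programme for eight weeks". Under Control group, the home programme is also daily and applies to both arms: "all participants are instructed to diligently adhere to the prescribed daily home exercise programme".
- **Self-rating.** Adherence monitoring opens with "A threshold for adherence is established for the experimental group, targeting participants to report a self-perceived rating of" at least 80%.
- **Frequency class.** The same section then says that diaries and self-report scales measure adherence to the home exercise programme over 3 months, and sorts patients by this rule: "classified as adhered ( $\geq 3$ times per week) or non-adhered ( $\leq 2$ times per week) based on the average frequency of sessions".
- **Use.** Specific Objective 4 is to analyse the "relationship between patient adherence to ULIT and improvements in hamstring strength and physical function over the 12-week rehabilitation period". It names no adherence measure and no cut-off. Statistical Analysis lists exercise adherence among the secondary outcome data and says only that it will be handled consistently with the primary result.

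**The concern.** The two frequency classes would be complementary if the quantity were a whole number of sessions in a single week. The protocol applies them to an average over many weeks, which will usually be fractional, so the classes do not cover the scale.

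The rule is also tied to a different quantity from the one in the objective. It counts home exercise over three months, a programme that both arms have. Objective 4 is about ULIT, which only the intervention arm receives and only for the last eight of the twelve weeks. Nothing in the rule separates ULIT sessions from the rest of the home programme.

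Finally, the section offers two yardsticks for the experimental arm, the self-rating and the frequency class, and does not say which one enters Objective 4. In an arm of 14 to 16 patients, each patient is 1/16 = 6.3% to 1/14 = 7.1% of the group. The handling of a few unclassified or discordant patients, if settled after the data are seen, could change what is reported about adherence.

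**Working it through.** The protocol gives no figure that depends on the adherence definition, so there is none to reproduce. The check is a count of which session totals each rule covers.

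**Inputs.** ULIT is daily for 8 weeks (Intervention Group). The adherence window is 3 months, taken here as 12 weeks (Adherence monitoring). The classes are at least 3 and at most 2 per week on average, and the rating threshold is 80% (Adherence monitoring). There are 14 evaluable and 16 randomised patients per arm (Sample Size). Assumption: one session a day, so at most 7 a week, giving totals of 0 to 56 over 8 weeks (57 possible values) and 0 to 84 over 12 weeks (85 possible values).

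**1. The gap.** A total *t* over *w* weeks has no class when 2 < *t*/*w* < 3, that is 2*w* < *t* < 3*w*.
- *w* = 8: 16 < *t* < 24, so *t* = 17 to 23 (averages 2.125 to 2.875), 7 of 57 totals.
- *w* = 12: 24 < *t* < 36, so *t* = 25 to 35, 11 of 85 totals.

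These are shares of possible totals, not of patients.

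**2. The two thresholds on one scale.** This step assumes that the self-rating reflects the share of daily sessions done, which the protocol does not state.
- The frequency cut-off as a share of daily: 3/7 = 42.9%.
- 80% of daily: 0.80 × 7 = 5.6 per week.
- Over 8 weeks: the frequency class needs 3 × 8 = 24 sessions; 80% of 56 is 44.8, so 45. Totals of 24 to 44 (averages 3.0 to 5.5; 21 of 57) are adherent by frequency but under 80%.
- Over 12 weeks: 3 × 12 = 36 against 80% of 84 = 67.2, so 68. Totals of 36 to 67 (32 of 85) are discordant.

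**3. How many patients this could touch.** Illustration only: 16 ULIT patients, each with the same assumed probability *p* of doing the session on any day, days independent, 56 days. The total is then binomial(56, *p*).

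| *p* | Expected unclassified (17–23) | Expected discordant (24–44) |
|---|---|---|
| 0.30 | 8.0 | 0.4 |
| 0.35 | 10.7 | 2.2 |
| 0.40 | 9.1 | 6.1 |
| 0.50 | 1.8 | 14.2 |
| 0.60 | 0.1 | 15.9 |
| 0.70 | 0.0 | 15.1 |

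The gap matters if typical completion is below about half of daily. Above that, the relation between the two thresholds matters more. The last column carries the assumption of step 2 as well.

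**4. What is measured against what is asked.**

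| | Frequency rule | Specific Objective 4 |
|---|---|---|
| Activity | Home exercise programme | ULIT |
| Who has it | Both arms | Intervention arm |
| Period of the activity | 3 months | Weeks 4 to 12 |

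**5. After closing the gap.** With at least 3 against below 3, the unclassified totals fall from 7 to 0 of 57 and from 11 to 0 of 85. This alone does not settle step 2 or step 4.

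**The case against.** The strongest defence is that the pieces do different jobs. Daily is the prescription, not a definition of adherence, and a cut-off below the full prescription is ordinary. The 80% is a self-perceived rating, set as a target for one arm; the frequency class describes the home programme for participants generally. Two instruments with different purposes need not agree, and the choice of variable for Objective 4 could sit in an analysis plan that is not shown. A three-month window also fits a home programme that runs for three months.

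Much of this stands. A reader might infer the following, and the documents do not support it:

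- *That there are three contradictory adherence rules.* There are two measures whose relation is unstated. The 5.6 against 3 comparison depends on the assumption in step 2, so a contradiction is not proven.
- *That a patient doing ULIT three times a week for all eight weeks would be classed non-adherent, because 24/12 = 2.0.* This assumes that ULIT-only sessions are averaged over twelve weeks, with nothing counted from the home programme. The protocol does not say that.
- *That Objective 4 cannot be answered.* It does not commit to the binary class, and weekly diaries are planned. The harm from the gap is conditional on the class being used.
- *That the primary result becomes arbitrary.* The protocol specifies intention-to-treat and plans no adherence-restricted primary analysis.
- *That patients in the gap are misclassified.* They are unclassified.

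The defence does not remove the gap, which is in the stated rule itself. Nor does it remove the mismatch between a home-programme measure and a ULIT objective. The section also calls the 80% a threshold for adherence, so treating it purely as an aspiration does not fit its own words.

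**Conclusion.** The point holds in a limited form and should be corrected. As written, the frequency rule leaves averages strictly between 2 and 3 without a class (17 to 23 sessions over 8 weeks, 25 to 35 over 12). It also does not isolate ULIT, and its relation to the 80% self-rating is unstated. The gap follows from the text alone; its size in session totals assumes at most one session a day. The size of any disagreement between the two thresholds further assumes that the rating tracks the share of daily sessions done, and the expected patient counts are illustrative only. The effect is confined to the adherence objective.

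**What to change.** For Specific Objective 4, define ULIT adherence as ULIT sessions completed divided by ULIT sessions prescribed in weeks 4 to 12, taken from the weekly online diary, and analyse it as a continuous variable. This uses all the information from a small arm and needs no class boundary. State that the diary records ULIT sessions separately from the rest of the home programme.

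If a binary class is also reported, use one cut-off and its complement. Say how the 80% self-rating and the frequency rule are reconciled, and what each is used for. Report home-programme adherence separately, for both arms. The choice of cut-off is for the investigators.

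The cost is protocol wording and possibly one diary item. The diary form is in an appendix that is not shown, so it cannot be confirmed here that ULIT sessions are already logged on their own.

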## **S1 Appendix. Study Protocol for Ethics Application**

### **EFFECT OF UPPER LIMB ISOMETRIC TRAINING ON HAMSTRING STRENGTH IN EARLY POSTOPERATIVE ANTERIOR CRUCIATE LIGAMENT RECONSTRUCTION PATIENTS: A RANDOMISED CONTROLLED TRIAL**

#### **Abstract**

This study aims to investigate the effects of upper limb isometric training (ULIT) combined with standard care of an anterior cruciate ligament reconstruction (ACLR) rehabilitation program on hamstring strength and physical function in the early-phase postoperative period. Early recovery of hamstring strength is critical for knee stability and functional rehabilitation post-ACL surgery. Hamstring strength deficits are prolonged issues in rehabilitation, with significant hamstring strength deficiencies in an early postoperative ACLR, especially using hamstring autograft, leading to functional limitations and an increased risk of secondary injuries. High knee muscle strength imbalances can hinder strength return in later stages. However, swelling, donor site pain, joint stiffness, and graft protection often neglect the direct activation of the hamstring in the early period. Also, clinical practice guidelines and consensus on early rehabilitation strategies are conflicting. While lower limb strengthening exercises are the mainstay of rehabilitation, this study explores the potential benefits of ULIT in promoting hamstring activation through the inter-limb posterior myofascial kinetic chain. This study hypothesise that participants receiving ULIT in addition to standard care will demonstrate better hamstring strength at 12 weeks post-operatively compared to those receiving standard care rehabilitation alone. A total of 32 patients who underwent ACLR with hamstring tendon autografts will be randomly assigned to either the ULIT group or a control group. The ULIT group performed upper limb isometric exercises in addition to standard postoperative rehabilitation, while the control group followed the standard rehabilitation protocol alone. We will measure hamstring and quadriceps strength using hand-held dynamometry at baseline (preoperative), 4, 8, and 12 weeks postoperatively. The primary outcome is the change in hamstring strength in the operated limb, while secondary outcomes included hamstring flexibility and patient-reported outcomes on symptoms, physical function and adherence. Statistical analysis will be conducted to compare the strength recovery between the two groups. It is believed that the results of this study will enhance knowledge about the global functional muscle concept, offer effective, safe, inexpensive, and feasible interventions, and promote further research on the interlimb connection of muscle activation and flexibility in heterologous muscle groups after ACLR.

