### **Blinding**

The individuals responsible for evaluating the results and managing the data are unaware of the assigned therapy. Participants will be informed that they will be assigned randomly to either the standard care group or the intervention group. The patients are reminded not to reveal their group allocation to the physician or medical officer who performed the outcome assessment. The details of ULIT are not recorded in the medical record. A sports physician and medical officer, who is blinded to the group allocation and located away from the physiotherapy outpatient unit, will assess all outcome measures at the Orthopaedic Clinic. If any participant notifies the assessor about their post-operative training session, this information will be

recorded and reported. The rationale for this notification will be documented when the randomization is revealed. An intention-to-treat analysis will be conducted.

Due to the nature of the treatments, it will not be possible for physiotherapists to be blinded to the treatment allocation of patients. The primary investigator (PI) and data analyst (not from the same departments) will be unaware of the treatment allocation as data will be evaluated using coded identification numbers. The central study coordinator (a staff who is not involved in intervention and outcome assessment) will be responsible for coding and re-coding the identification numbers.

A half-day training workshop for blinded assessors and treating physiotherapists will be conducted before this study commences to enhance data quality and protocol adherence, reduce the bias risk of assessment and treatment, and increase the confidence and competence of the investigator.

To assure the overall standard and credibility of this clinical study, the process of disclosing the assigned treatment to participants will only be done in exceptional instances, for instance when there is a risk of harm, and when knowing the real treatment becomes essential for the participant's ongoing care. Before disclosing the group allocation, the PI will determine the necessity and amount of un-blinding. The allocation will remain confidential and will not be revealed to other study team members. If any code breaks occur, the PI will report it with the justifications.

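### A physician is to rate rehabilitation adherence (SIRAS) at the clinic where blinded physicians test strength, and the protocol does not keep the two roles apart

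*Protocol*

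**What the plan says.** Adherence monitoring: SIRAS "is administered by a physician and physiotherapist to assess the level of adherence of all patients to the rehabilitation procedure in both study groups". The rating is made "at the Orthopaedic Clinic and physiotherapy outpatient rehabilitation session".

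Blinding: the assessors are described as "A sports physician and medical officer, who is blinded to the group allocation and located away from the physiotherapy outpatient unit", and they "will assess all outcome measures at the Orthopaedic Clinic". Patients are asked not to tell these assessors their group, ULIT details are kept out of the medical record, and a patient's mention of post-operative training to an assessor has to be logged and reported.

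Data Collection: "The blinded assessors will give all tests and questionnaires in person, ensuring participant consistency". On the strength test, the same section says: "The assessor will consistently give instruction and verbal encouragement".

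Adherence is counted among the outcomes. The Abstract states that "secondary outcomes included hamstring flexibility and patient-reported outcomes on symptoms, physical function and adherence", and Statistical Analysis includes exercise adherence in the secondary outcome data. Specific Objective 4 relates adherence to gains in strength and function.

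**The concern.** The two arms differ only in whether ULIT is added to standard care. A conversation about how well a patient has kept to the programme is therefore one in which the allocation can easily come out. If the physician holding that conversation also runs the strength test, the assessor may learn the group.

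The primary outcome is exposed to this. It is a maximal voluntary contraction, recorded while the assessor instructs and encourages the patient, so the assessor's expectation could affect the effort obtained. Study Design labels the trial single-blinded at the assessor, the treating physiotherapists cannot be blinded, and patients know which exercises they do. Assessor blinding is thus the main protection at the moment of measurement. Coding the data for the analyst cannot repair a measurement that was already biased when it was taken.

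**Working it through.** No arithmetic applies to the role conflict. It is checked by setting the sections side by side.

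1. **Who rates SIRAS, and where.** A physician and a physiotherapist, for patients in both arms, at the Orthopaedic Clinic and at the physiotherapy session (Adherence monitoring).

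2. **Who the blinded assessors are, and where they work.** A sports physician and a medical officer, at the Orthopaedic Clinic, away from the physiotherapy unit (Blinding).

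3. **What the blinded assessors cover.** Every outcome measure (Blinding) and every test and questionnaire (Data Collection). Neither sentence makes an exception for adherence.

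4. **Whether adherence is an outcome.** Yes, in the Abstract and in Statistical Analysis.

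5. **Putting 1 to 4 together.** There are two possibilities.
   - The SIRAS physician is a blinded assessor. The person whose blinding matters most then rates adherence to the programme.
   - The SIRAS physician is someone else. Adherence monitoring then conflicts with the two sentences in step 3, because someone other than the blinded assessors measures an outcome.

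   Either way the sections have to be reconciled. The text at hand does not name a separate physician, set the order of SIRAS and the strength test, or limit what the physician may ask or see.

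6. **Whether the rating can disclose the group.** The Blinding section treats talk of post-operative training to the assessor as an event to record. An adherence rating invites such talk. The assessor sits away from the unit where sessions take place, so a rating would plausibly rest on asking the patient or on reports from unblinded physiotherapists.

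7. **How disclosure would reach the primary outcome.** Allocation follows baseline testing, so the preoperative test is safe. Strength is then tested at weeks 4, 8 and 12, and ULIT starts in the fourth week. A disclosure at one visit carries over to later ones. Statistical Analysis takes the change from week 4 to week 12 as the main outcome measure. Let b4 and b12 be the average shifts in recorded ULIT-arm force caused by the assessor's knowledge at those visits, with none in the control arm. The between-group difference in change is then shifted by b12 − b4. The shift cancels only if the two are equal, which is unlikely if knowledge builds up over the visits. The protocol gives no value for either term.

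**The case against.** The strongest reply is that the overlap is inferred. Adherence monitoring says only that a physician does the rating, and the Orthopaedic Clinic has other doctors, including surgeons and those running routine follow-up. Adherence also has its own section, apart from the secondary outcomes. Some of it is collected by physiotherapists' phone calls and online diaries, so the sentence giving the assessors every outcome cannot be meant quite literally. This stands as a limit: the documents do not state that the two physicians are the same person. It does not remove the point, because the other reading leaves the sections in conflict and nothing separates the roles.

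Secondly, SIRAS is described as a measure of clinic-based adherence and is used alike in both arms, while ULIT is largely a home exercise recorded by diary. A blinded clinician might rate general adherence without ULIT being mentioned. This also stands in part. A reader might infer that the rater has to discuss what was prescribed and so must become unblinded. The documents do not support that, since the form is in Appendix E, which is not shown. They support only that it can happen.

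Thirdly, there are safeguards: the reminder to patients, the silence of the medical record, the logging of disclosures, assessor training, and consistent instructions for the test. They lower the risk and make some disclosures visible. None of them deals with an assessor who is also asked to rate adherence.

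**Conclusion.** The point holds as a conflict between sections with a plausible route to unblinding. It rests on two assumptions: that the SIRAS physician at the clinic is one of the blinded assessors, or could be, and that rating adherence sometimes brings up ULIT. Both are reasonable on the text, and neither is stated there.

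Two stronger conclusions should be resisted. A reader might infer that assessor blinding is the only blinding in the trial. It is not: Randomisation and Allocation and Blinding also keep data analysts unaware of the allocation, and Blinding adds the principal investigator and those managing the data. A reader might also want an inflated false-positive rate. The protocol offers no basis for one. It gives no size for assessor bias, and Sample Size states a standard deviation but no target difference. It also describes the outcome there as a symmetry index, while the table beneath it gives peak torque from a cited study. The size of the bias is therefore unknown. The change is worth making because it is cheap and protects an effort-dependent primary measurement.

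**What to change.** In Adherence monitoring, have SIRAS completed by the treating physiotherapist, who already knows the allocation, or by a physician who does no outcome testing, and say which. State that SIRAS forms and exercise diaries are kept from the outcome assessors until their assessments are complete. In Blinding and in Data Collection, amend the sentences that say the assessors "will assess all outcome measures at the Orthopaedic Clinic" and "The blinded assessors will give all tests and questionnaires in person, ensuring participant consistency" so that both exclude adherence.

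Rating SIRAS after the strength test at each visit would be weaker, because it protects that visit but not later ones.

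The cost is a few sentences of wording. With the physiotherapist option there are no extra visits or staff. What is lost is the assessor-physician's SIRAS rating. The adherence rating used for Specific Objective 4 may then come only from an unblinded rater, alongside the patients' diaries, and the report should say so. Using a separate physician keeps a physician's rating but requires one who does no outcome testing.
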